### 3 Study procedures

***3.1 Entry criteria***

•All adult patients (≥16 years old) with a clinical diagnosis of generalized tetanus [as opposed to localized tetanus] admitted to the ICU at the Hospital for Tropical Diseases, Ho Chi Minh City, Vietnam.

***3.2 Exclusion criteria***

•Contra-indication to use of human or equine antitoxin•Contra-indication to lumbar puncture•Already receiving mechanical ventilation or expected to require this before intrathecal injection can be given•Pregnancy•Informed consent not obtained

***3.3 Patient identification.*** All patients with generalized tetanus will be identified by doctors working in the Hospital for Tropical Diseases ICU.

***3.4 Informed consent.*** Informed consent will be taken by the attending doctors, all of whom will receive specific training in the study and Good Clinical Practice and will be authorised to take consent by the trial principal investigator (see
Supplementary File 3). These doctors will also assess whether or not the patient has mental capacity to provide informed consent. If the doctor judges that the patient does not have this capacity, they will obtain informed consent from the patient’s representative (usually a relative). It will be made completely and unambiguously clear that the patient (or their representative) is free to refuse to participate in all or any aspect of the trial, at any time and for any reason, without incurring any penalty or affecting their treatment.

The informed consent form will be presented to the participants or representatives detailing no less than: the exact nature of the study; the implications and constraints of the protocol; the known side effects, risks involved and alternatives to taking part. Those who refuse consent will be treated as per the best available standard of care and will not have any study related procedures performed. 

The patient or their representative must personally sign and date two of the latest approved versions of the informed consent form. The study staff will also sign and date the two copies. The patient/representative will receive one copy.

If the patient/representative is illiterate, a witness who is not a member of the study staff will be present during the informed consent discussion. The informed consent form will be read to the patient/representative in the presence of the witness. If the patient/representative agrees to participate, the form will be signed and dated by the witness. If the patient is a minor (defined as < 18 years of age) assent will need to be obtained in addition to parental or guardian consent.

If consent is provided by a representative and the patient regains the capacity to consider participation during the study period, the patient should be consulted and informed consent to continue the study obtained. If the patient refuses to give informed consent to participate they will be withdrawn from the study without compromise to their clinical care.

***3.5 Screening and eligibility assessment.*** Potential participants will be screened by the attending physicians. Screening will include clinical diagnosis and inspection of clinical notes. Results of any tests performed for clinical care during this illness episode may be used for the purposes of screening. A screening log will be kept on the ward, with a record of all patients screened and how they met/did not meet the study entry and exclusion criteria. No identifying details such as name will be recorded in this log. Patients who do not meet the study criteria will be informed as such and treated as per best available clinical care.

***3.6 Randomisation and treatment allocation.*** Randomisation will be 1:1:1:1 to the four treatment arms (intrathecal treatment and human intramuscular treatment, intrathecal treatment and equine intramuscular treatment, sham procedure and human intramuscular treatment, sham procedure and equine intramuscular treatment). Randomization will be based on a computer-based randomization list using block randomization with variable blocks lengths of 8 and 12 without stratification.

Only the study pharmacist who is not otherwise involved in the trial will have access to the randomization list and will use it to prepare treatment packages with sequential numbering. All treatment packs will be identical externally. Each patient will receive the next sequential package, which will be prepared in advance and available on the ward and stored appropriately. Each treatment pack will contain the appropriate study treatment. 

***3.7 Study treatment.*** The standard treatment group will receive intramuscular treatment with 21,000 units equine antiserum (Viet Nam) or 3000 IU human antitoxin (CSL Behring) including a 0.05ml test dose (i.e. 75 units equine antitoxin or 12.5 IU human antitoxin). These are the recommended doses for treatment of tetanus. This equates to a total 14ml equine antitoxin and 12 ml human antitoxin. The intrathecal intervention group will receive 500 IU (total 2 ml) human tetanus antitoxin intrathecally. Both groups will receive this treatment as soon as possible after enrolment, with all antitoxin aimed to be given within 6 hours of admission. Patients who have been given a treatment dose of intramuscular antitoxin before admission will have the intramuscular injection omitted. The dose of 500 IU has been chosen on the basis of previous studies which have used between 250 and 1000 IU, but possible benefit of doses > 250 IU human antitoxin were noted in one meta-analysis
^20^. 250 IU doses have been used without reports of harm in neonates. Equally no difference in benefit was observed in a study comparing 200 and 1500 units of equine antitoxin
^14^.

Both equine and human preparations will be stored between 2 and 8°C. Prepared study packs will also be stored at this temperature until used. All receipt, transfers, dispensing, administration and return of study drug will be accounted for by the trial pharmacist. Study drug will be prescribed and administered by standard hospital and Oxford University Clinical Research Unit (OUCRU) procedures. Ward nurses trained in study procedures will be responsible for safe storage and in-hospital administration.

All other treatments will follow standard management of tetanus at the Hospital for Tropical Diseases. This will comprise of antibiotics, spasm control and cardiovascular modulation as current protocols dictate. Sedation will follow standard protocol: diazepam, following tracheostomy magnesium sulphate, then paralysis with pipecuronium.

***3.8 Blinding procedures.*** Investigators and attending doctors will be blinded to treatment allocation. Only trained and knowledgeable staff, trained in Good Clinical Practice and the protocol, and delegated in the delegation log will be able to perform study procedures. This will be as follows:

•The attending doctors will contact the independent study doctor (see below) when a patient has entered the study. The independent study doctor who does not have normal duties on the ICU nor responsibility for day-to-day care of tetanus patients will access the treatment pack and allocation to ascertain whether the additional intrathecal injection or a sham procedure is to be performed.•The independent study doctor or a similarly independent study nurse will deliver the initial intramuscular injection of antitoxin, thus doctors and nurses treating patients will not be aware of initial intramuscular treatment.•The intrathecal injection or sham procedure will be given by the independent doctor behind screens. The sham procedure will involve placing a dressing over the lumbar area in an identical way to the procedure after true lumbar puncture. In this way doctors and nurses treating the patient will not be aware of the intrathecal treatment. Patients will be asked not to discuss their given treatment with doctors or nurses caring for them.•All patients will be kept in the supine position for 4 hours after intrathecal injection or sham procedure, in keeping with normal procedure following lumbar puncture. Supine position of tetanus patients has been shown to be non-inferior to semi-recumbent
^25^, therefore we do not think this is deleterious to patient care.•No open record of the lumbar puncture procedure or study drug administered will be kept in the clinical notes. A sealed record of the intrathecal injection procedure will be placed in a sealed envelope in the patients notes to be opened if the attending clinicians feel necessary.•Daily management decisions will be made by attending doctors (responsible for day-to-day patient care) following normal protocols and using defined criteria for mechanical ventilation.

***3.9 Baseline assessment.*** This will consist of basic clinical and demographic data, including SOFA score and Tetanus Severity Score. If a wound is present swabs will be taken for
*Clostridium tetani* culture. This will provide supportive data for the diagnosis of tetanus. Bacterial DNA may be stored for later analysis.

Cerebrospinal fluid (CSF) that has been withdrawn for antitoxin administration will be stored for analysis of tetanus toxin and antitoxin concentration.

Residual samples from these analyses may be stored for use in future studies.

***3.10 Subsequent assessments.*** Whilst the patient is in ICU, daily treatment interventions (i.e. tracheostomy or mechanical ventilation), doses of predefined drugs, heart rate, blood pressure, respiratory rate, SpO
_2_ and temperature will be recorded. Incidence of predefined hospital-acquired infection and new antibiotic prescriptions will be recorded.

Daily doses of diazepam will continue to be recorded after discharge from ICU until cessation of therapy.

Urinary catecholamines will be measured from a 24-hour collection taken on day 5.

•Criteria for tracheostomy are: laryngeal spasm or sputum retention; or requirement for muscle paralysis and mechanical ventilation due to uncontrolled spasm.

***3.11 Discontinuation of treatment and participation.*** If a patient or the representative, who has given consent on their behalf, chooses to discontinue trial treatment, they should be followed up (providing they are willing) and encouraged to follow the study procedures in lieu of withdrawing from the trial. If they do not wish to remain on trial follow-up, however, their decision will be respected and the patient will be withdrawn from the trial completely. This will be recorded on the OUTCOME Case Report Form (see
Supplementary File 4). The reason for the patient withdrawing should be ascertained wherever possible. Prior to withdrawing completely from the trial, the patient will be invited to have assessments performed as appropriate for the final visit although they would be at liberty to refuse any or all individual components of the assessment.

In addition, the investigator may decide to stop the study intervention if they feel it would not be in the patient’s best interests. Patients will be followed as per protocol. Reasons for stopping the intervention would include, but are not limited to:

•Pregnancy•Ineligibility (either arising during the study or retrospective having been overlooked at screening e.g. an alternative diagnosis to tetanus being confirmed)•Significant non-compliance with treatment regimen or study requirements•Allergic reaction to intramuscular injection•Inability to administer intrathecal antitoxin 

***3.12 Unblinding.*** Unblinding means revealing the identity of the study treatment (i.e. intrathecal or intramuscular only). Study treatment should only be unblinded if knowing the treatment that a patient has been allocated will result in a change in the patient’s management. The decision whether or not to unblind should be discussed with the Principal Investigator. Unblinded treatment allocation information will be available in opaque, tamper-proof envelopes held securely at each site and available at all times. A record of the lumbar puncture procedure will be available in a sealed envelope in the patients’ notes. The responsibility to approve unblinding will be assigned to dedicated site staff. Access to treatment allocation information should only be given with the approval of one of these dedicated staff. Unblinding will be documented in the Case Report Form. 

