Current treatment for tetanus in Vietnam consists of intramuscular equine antitoxin. One randomized controlled trial has compared equine antitoxin in the treatment of tetanus with human antitoxin (human tetanus immunoglobulin) in a total of 130 neonates. There was no difference in complications and no side effects attributable to antitoxin were apparent in either group
^23^. Currently in Vietnam, human antitoxin is more expensive and is only just becoming available, although it is the product recommended by the World Health Organization due to a theoretical improved side-effect profile (with a reduced risk of serum sickness and anaphylactic reactions)
^7,
24^. Better understanding of the side-effect profile and use of human versus equine preparations would be useful in Vietnam and many low and middle income countries when choosing which preparation to use. 

The primary aim of this study is to assess the benefit of additional intrathecal tetanus antitoxin to intramuscular regimens. However, due to the factorial design of this study, we are also able to compare the side effect profile of equine and human antitoxin.

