### 2 Study design

We will conduct a randomised partially-blinded controlled 2#215;2 factorial trial. First, adults admitted to the ICU at the Hospital for Tropical Diseases will be randomized to receive either human (3000 IU) or equine (21,000 units) intramuscular antitoxin. Second, participants will be randomized to receive either standard treatment with intramuscular antitoxin alone or with the addition of 500 IU intrathecal human antitoxin. Patients with contra-indications to lumbar puncture or antitoxin treatment will be excluded. Patients who have already received a treatment dose of intramuscular antitoxin will have the intramuscular injection omitted.

All patients will receive other standard tetanus treatment as deemed necessary by the attending physicians. Spasms will be treated with benzodiazepines as first-line therapy. Patients with spasms not controlled with benzodiazepines will receive tracheostomy, paralysis, magnesium sulphate and mechanical ventilation. Heart rate, blood pressure, respiratory rate, temperature, oxygen saturation and daily drug use will be recorded throughout the ICU stay. Patients will be followed following discharge from hospital until 240 days for disability/ death.

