### 5 Statistics

***5.1 Sample size justification.*** Data from the Hospital for Tropical Diseases in 2013 showed that 40% of patients with tetanus required ventilation (43 out of 110 in a 6 month period). However an estimated 4–6% of patients did not have generalized tetanus and would be excluded from study entry. Therefore we estimate that 45% of study subjects without intrathecal treatment will require mechanical ventilation in our study. The main comparison of this 2x2 factorial trial is the comparison between subjects receiving intrathecal human antitoxin versus those without intrathecal treatment. To detect an absolute risk reduction for mechanical ventilation due to intrathecal treatment by 17% (from 45% to 28%) with 80% power at the two-sided 5% significance level, 250 subjects are required. To account for some protocol violations and losses to follow-up, the trial will randomize a total of 272 patients (68 in each of the four treatment arms in the 2x2 factorial trial). Should the ventilation rate in the control arm be lower than anticipated, this samples size will also detect a reduction from 40% to 24% with 80% power.

Regarding the secondary endpoint of ICU stay, median (interquartile-range) duration of ICU stay from historic data of 111 tetanus admitted to the Hospital for Tropical Diseases was 13
^4–
22^ days. Based on simulation and these historical data, 272 subjects will provide 88% power to detect a relative reduction in the ICU stay by 25% using the Cox proportional hazards model.

***5.2 Description of statistical methods.*** The primary analysis population for all analysis is the full analysis population containing all randomized patients. Patients will be analyzed according to their randomized arm (intention-to-treat). Analyses for the primary endpoint will be repeated on the per protocol population which excludes the following patients: patients not receiving the randomized intervention and other major violations of inclusion/exclusion criteria or study procedures. 

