### 8 Ethics

***8.1 Ethical and regulatory guidelines.*** The Principal Investigator will ensure that this study is conducted in accordance with the principles of the Declaration of Helsinki (Seoul 2008) and the terms of approval of the appropriate ethics committees. The Investigator will ensure that this study is conducted in full conformity with relevant regulations and with the International Council for Harmonization for Good Clinical Practice July 1996.

***8.2 Ethical review.*** This protocol and all associated informed consent forms has been approved by the Ethics Committee of the Hospital for Tropical Diseases (816/QD BVBND), Oxford Tropical Research Ethics Committee
^16,
17^ and the Viet Nam Ministry of Health (1122/QD-BYT). The investigators will submit and obtain, where necessary, approval from the above parties for all substantial amendments to the original approved documents.

***8.3 Risks and benefits.*** All patients will receive the best available standard-of-care in Vietnam. Side effects associated with the use of equine anti-toxin at the Hospital for Tropical Diseases are infrequent (< 1%). Human immunoglobulin is reported to be associated with an improved safety profile compared to equine preparations
^26^.

Risks of procedures involved in the study

Risk of intramuscular injection (all groups), which are minimal. All tetanus patients currently receive intramuscular injection of antitoxin; therefore there is no additional risk associated with participating in this study. Intramuscular injection of human antitoxin is reported to be associated with fewer adverse reactions than the current standard equine antitoxin.

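### Patients given antitoxin before admission get no trial intramuscular product but stay in the human-versus-equine comparison by allocated arm, which shrinks any true difference

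*Protocol article*

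**What the plan says.** The omission rule appears twice. Section 2 says "Patients who have already received a treatment dose of intramuscular antitoxin will have the intramuscular injection omitted", and section 3.7 says "Patients who have been given a treatment dose of intramuscular antitoxin before admission will have the intramuscular injection omitted". Prior treatment is not an exclusion: the only product-related criterion in section 3.2 is "Contra-indication to use of human or equine antitoxin". Section 3.6 states "Randomisation will be 1:1:1:1 to the four treatment arms", in permuted blocks without stratification, so pre-treated patients also receive a human or equine allocation.

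Section 5.2 applies the full analysis population to every analysis: "Patients will be analyzed according to their randomized arm (intention-to-treat". The same section plans human versus equine as a secondary comparison. Section 1.2 makes informing the choice between the two products a secondary objective, and the Introduction gives side effects as the purpose: "we are also able to compare the side effect profile of equine and human antitoxin".

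Two provisions in section 5.2 bear on the problem. The primary-endpoint analyses are repeated in a per-protocol population that leaves out patients who did not receive their randomised intervention. Antitoxin before admission is also one of the pre-defined variables for interaction tests.

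**The concern.** A pre-treated patient allocated to human product and one allocated to equine product are treated alike intramuscularly: neither gets a trial injection, and each carries whatever was given beforehand. The protocol does not record what that was. The Introduction's "Current treatment for tetanus in Vietnam consists of intramuscular equine antitoxin" makes equine product likely in both arms. Within this stratum the comparison therefore carries no information on human versus equine product, yet it is averaged into the result.

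This differs from ordinary non-adherence, which intention-to-treat is meant to absorb. Here the protocol itself directs that the allocated product is not given, for a reason already settled before randomisation. What is at stake is the third secondary objective: the reported difference between products would be biased towards zero by an amount set by referral practice, not by the products.

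**Working it through.** **Inputs from the protocol (section 5.1).** Ventilation 45% versus 28%; two-sided 5% level; 80% power; 250 evaluable and 272 randomised, 68 per cell, hence 136 per level of each factor.

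**Input not given.** The pre-treated share f. Values of 10%, 20%, 30% and 50% are assumed.

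**Step 1: reproduce the protocol's figure.** With mean proportion p̄ = (0.45 + 0.28)/2 = 0.365,

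n per group = [1.96·√(2p̄(1-p̄)) + 0.842·√(p1(1-p1) + p2(1-p2))]² / (p1-p2)² = [1.96 × 0.681 + 0.842 × 0.670]² / 0.17² = 124.7, so 125 per group and 250 in total. This matches. With 136 per level, power is 83%.

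**Step 2: dilution.** Randomisation makes the expected pre-treated share equal in both arms. With no human-equine difference among the pre-treated,

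expected difference in all randomised = (1-f)·Δ + f·0 = (1-f)·Δ.

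**Step 3: illustration on a common outcome.** The protocol states no effect for human versus equine, so its 17-point effect is borrowed, with 45% as the higher risk in both strata. Power is

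Φ{[√n·d - 1.96·√(2p̄(1-p̄))] / √(p1(1-p1) + p2(1-p2))}.

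At f = 20%:
- All randomised: n = 136, d = 0.136 (45% versus 31.4%). (1.586 - 1.347)/0.680 = 0.352, so power is 64%.
- Not pre-treated: n = 136 × 0.8 = 108.8, d = 0.17. (1.773 - 1.334)/0.670 = 0.655, so power is 74%.

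| Assumed f | Difference, all randomised | Power, all randomised | Difference, not pre-treated | Power, not pre-treated |
|---|---|---|---|---|
| 0 | 17.0 points | 83% | 17.0 points | 83% |
| 10% | 15.3 points | 74% | 17.0 points | 79% |
| 20% | 13.6 points | 64% | 17.0 points | 74% |
| 30% | 11.9 points | 52% | 17.0 points | 69% |
| 50% | 8.5 points | 30% | 17.0 points | 54% |

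The restricted set has fewer patients but more power at every f above zero.

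**Step 4: reactions caused only by the injection.** Assume 10% versus 2% in injected patients and none in pre-treated patients. The absolute difference falls from 8.0 points to 6.4 (f = 20%) or 4.0 (f = 50%). Power in all randomised patients is 70% and 49%; in the restricted set it is 70% and 50%. With Fisher's exact test at 6% versus 0% and f = 20%, six events against none are needed either way, and power is 64.0% (136 per arm) against 64.4% (109 per arm). Here restriction corrects the absolute risk but leaves power almost unchanged. The risk ratio is not diluted unless background events occur in both arms.

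**The case against.** The strongest reply is that the plan already handles much of this. Read literally, the per-protocol repeat removes pre-treated patients from the human-versus-equine comparison of mechanical ventilation, and the interaction test looks at the stratum directly. Section 5.2 also says that other binary endpoints follow the primary-outcome approach, so the interaction test could be taken to reach adverse events. This stands as partial mitigation. The main analysis remains diluted, however, and the per-protocol repeat is stated for the primary endpoint only. Its wording has a side effect too: it could drop pre-treated patients from the intrathecal comparison, although they were managed as the protocol directs.

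It is also fair that analysing all randomised patients is conventional, and that supplementary sets are often left to an analysis plan. But the protocol fixes the primary population for all analyses, so this choice is made here.

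Four stronger readings are tempting and are not supported:
- **That the primary result is diluted.** It is not; pre-treated patients still receive their intrathecal or sham allocation.
- **That the required sample size rises by 1/(1-f)².** That compares with a trial containing no pre-treated patients, which no analysis can deliver. Against the restricted analysis the penalty is about 1/(1-f).
- **That the safety comparison fails a power claim.** Section 8.3 does say "Side effects associated with the use of equine anti-toxin at the Hospital for Tropical Diseases are infrequent (< 1%), but the protocol states no power for this comparison, and that figure is past hospital experience rather than a planning rate for actively monitored events.
- **That pre-treated patients had no antitoxin, or certainly equine.** They had a treatment dose of unstated type, and those allocated to intrathecal treatment also receive human antitoxin by that route.

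**Conclusion.** The point holds for the human-versus-equine comparison only. As written, its main analysis estimates (1-f) of the true absolute difference between products. This follows from the omission rule, the absence of an exclusion, and the all-randomised population; it assumes only that the intramuscular label has no effect where no trial injection is given. The size cannot be fixed because f is not stated. On the borrowed 17-point effect, the loss against the restricted analysis is 5 power points at f = 10% (79% to 74%) and 24 at f = 50% (54% to 30%), assuming the same underlying risk in both strata. For injection-only reactions the issue is bias in the absolute risk, not power. The correction is worth making before analysis.

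**What to change.** In section 5.2, state that:
- the main human-versus-equine comparison, for efficacy endpoints and adverse events, is made in randomised patients with no treatment dose of intramuscular antitoxin before admission, analysed by allocated arm;
- the all-randomised result is reported alongside, with the number pre-treated in each arm;
- intrathecal versus sham keeps all randomised patients, and its per-protocol set does not drop a patient merely because the intramuscular injection was omitted under the protocol's own rule.

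Prior treatment is fixed before randomisation and is already a subgroup variable, so the restricted comparison remains a randomised one. The variable should be defined to match the omission rule, that is, a treatment dose.

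The cost is analysis wording and a smaller set for this one comparison, 272 × (1-f) patients in expectation. No treatment rule, procedure or recruitment target changes. For reactions caused only by the injection, the gain is an undiluted absolute risk rather than a more powerful test.
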